#### Secondary endpoints

ORR at day 14Proportion of patients in each arm who achieve a PR or CR without requirement for additional systemic IST, persisting for at least 4 consecutive weeks within 8 weeks after randomization.Time to response, defined as time from randomization to the date of first documentation PR or CR. Death or relapse/progression of underlying hematologic disease without prior response will be considered to be a competing event. Comparison of treatment arms is conducted until day 28 only, as crossover to ruxolitinib is offered to non-responders then.Rate of patients with treatment failure until day 28 after randomization.Duration of response, assessed for responders only by calculating the time from first response to the date of first observation of aGvHD relapse/progression or the date of additional IST for GvHD. Onset of chronic GvHD (cGvHD) or death without prior observation of aGvHD relapse or progression is considered to be a competing events, and observations where neither occurred are treated as censored observations.Overall survival (OS) defined as time from randomization to the date of death from any cause.Event-free survival (EFS) defined as the time from randomization to the date of recurrence of underlying hematologic disease, graft failure or death due to any causeNRM defined as the time from randomization to the date of death not preceded by hematologic disease recurrence. Hematologic disease recurrence / progression are considered to be a competing event.Failure-free survival (FFS) is defined as the time from randomization to recurrence of underlying hematologic disease, graft failure, NRM or addition of new systemic IST for GvHD. Onset of cGvHD is considered as a competing event.Rate of patients in whom failure to taper steroids below methylprednisolone dose of 0.5 mg/kg/day (or equivalent < 0.6 mg/kg/day of prednisone /prednisolone) was observed within 56 days after randomization OR addition of any new IST for GvHD due to failure to taper steroids below methylprednisolone dose of 0.5 mg/kg/day (or equivalent < 0.6 mg/kg/day of prednisone/prednisolone)Rate of patients discontinued ruxolitinib treatment for at least 4 weeks.Discontinuation rate of steroid therapy for at least 4 weeks.ORR at day 14 in this group, defined as proportion of patients demonstrating PR or CR without requirement for additional systemic IST at day 14 after date of cross over from BAT alone to ruxolitinib/BAT.ORR at day 28 in this group, defined as proportion of patients demonstrating PR or CR without requirement for additional systemic IST at day 28 after date of cross over from BAT alone to ruxolitinib/BAT.Proportion of patients who achieve a PR or CR without requirement for additional systemic IST, persisting for at least 4 consecutive weeks within 8 weeks after the date of cross over from BAT only to ruxolitinib/BAT.Cumulative steroid dose until day 56.Reduction of GvHD blood biomarkers on day 8 randomization.Relapse rate of underlying hematologic disease, calculated as incidence rate, time from randomization to the date of relapse diagnosis. Death without prior relapse will be considered as a competing event.Graft failure incidence rates, calculated as time from randomization to the date of graft failure diagnosis. Death without prior graft failure will be considered as a competing event.Quality of life (QoL): EORTC QLQ-C30 and EORTC QLQ-C29.Time from randomization to the start date of any cGvHD. Hematologic relapse/progression and death without prior cGvHD will be considered as competing events.Type, frequency, severity and relationship of adverse events to investigational product, engraftment, infections.Frequency of CMV reactivation.Number of nights in hospital.

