### Study treatment

#### Ruxolitinib treatment

Ruxolitinib treatment will be administered for 6 months or as long as the patient experiences benefit from treatment with ruxolitinib. In this case treatment might be prolonged at the discretion of the investigator. In patients with CR or stable PR (≥ 4 weeks) and off steroids, ruxolitinib will be tapered. Patients randomized to ruxolitinib and BAT who do not meet the primary endpoint at day 28 will discontinue ruxolitinib and will be treated at the discretion of the investigator. In case of relapse of underlying malignancy, the study treatment will be permanently discontinued.

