## Discussion

Retrospective data suggest that JAK1/2 inhibition with ruxolitinib can induce clinically meaningful and ongoing responses in heavily pretreated patients with acute and chronic steroid-refractory GvHD. To confirm these observations, single arm (NCT02953678, NCT02997280, NCT02806375) and randomized prospective trials (NCT02913261, NCT03112603) are ongoing. To establish the benefit of ruxolitinib versus best available treatment (BAT), a randomized design is needed. This trial (NCT02396628) is intended to examine ruxolitinib as add-on to BAT versus BAT alone. Thus, previously started GvHD treatments can be continued in addition to ruxolitinib at the discretion of the investigator. There is no limitation of previous and concomitant lines of aGvHD treatments, since patients in our retrospective series had a median number of three (range: 1–7) previous GvHD therapies [19]. This trial allows cross-over from BAT to BAT and ruxolitinib for patients receiving BAT not achieving the primary endpoint at day 28, with loss of response after day 28 or failure to taper steroids. However in both arms, in case of deterioration of GvHD within the first 14 days or lack of improvement, treatment may be permanently discontinued at the discretion of the investigator. In this case, the protocol recommends individual case-by-case discussion with the sponsor. Patients in the ruxolitinib arm not meeting the primary endpoint at day 28 will discontinue ruxolitinib and will be treated at the discretion of the investigator, although in our retrospective analysis we observed responses in aGvHD up to week eleven of treatment. The duration of treatment will be 6 months or as long as the patient experiences benefit from ruxolitinib treatment. In case of CR or stable PR (≥ 4 weeks) and off steroids, ruxolitinib is slowly tapered starting at day 56. In case of reappearance of GvHD signs during tapering or after tapering has been completed, the dose may be increased or treatment with ruxolitinib may be reinstituted. Hematological adverse events will be recorded but however, dose interruptions and dose reductions during treatment due to hematological adverse events are optional and as required in the investigators opinion. Also, baseline cytopenias are not prohibitive for inclusion. The protocol includes dose modifications for drug-related, non-hematological adverse events that are not GvHD related. As a unique feature of this trial, study drug is provided by regular prescription beyond approved indication. Accounting of study drug was approved by the Gemeinsame Bundesausschuss (GBA) according to § 35c Abs. 2 SGB V.

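### The new-IST component of failure-free survival can count the same post-response GvHD flare as an event on BAT and as no event on ruxolitinib

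*Protocol article*

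**What the plan says.** Under Secondary endpoints, FFS runs from randomization to recurrence of the haematologic disease, "graft failure, NRM or addition of new systemic IST for GvHD", with onset of chronic GvHD as a competing event. Relapse or progression of acute GvHD is not listed as a failure.

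The Discussion gives the treatment paths. Crossover to BAT plus ruxolitinib is allowed for BAT patients "not achieving the primary endpoint at day 28, with loss of response after day 28 or failure to taper steroids". In the ruxolitinib arm, on "reappearance of GvHD signs during tapering or after tapering has been completed, the dose may be increased or treatment with ruxolitinib may be reinstituted". Tapering is for patients in CR or stable PR who are off steroids, and starts at day 56.

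Two neighbouring endpoints are protected against these paths. Duration of response ends at "the date of first observation of aGvHD relapse/progression or the date of additional IST for GvHD", so a flare counts in either arm whatever is done about it. For time to response, the article says: "Comparison of treatment arms is conducted until day 28 only, as crossover to ruxolitinib is offered to non-responders then". FFS has neither safeguard. Nothing in the article says whether crossover, or a restart of ruxolitinib, counts as new IST.

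Under Statistical planning, the types of FFS failure are analysed separately, each with the other types and chronic GvHD as competing events.

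**The concern.** In this component, FFS records the reaction to a flare and not the flare itself, and it records the reaction only if the agent is new. The two arms are offered different reactions. Ruxolitinib is new to a BAT patient and not new to a patient randomized to it. Two patients with the same loss of response can therefore be classified differently because of the arm they are in.

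The cumulative incidence of new IST could then differ between arms when GvHD control does not, or understate flares on ruxolitinib. FFS would partly measure which arm still had a drug in reserve.

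**Working it through.** **Plan's own figure.** The article gives no figure for FFS. Its sample size reproduces, which confirms the response rates and arm size used below. One-sided α = 0.05, power 80%, 30% vs 50%, pooled variance, no continuity correction:

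n = [1.645·√(2·0.4·0.6) + 0.842·√(0.3·0.7 + 0.5·0.5)]² / 0.2² ≈ 73.1, so 74 per arm and 148 in total. Increased by 8%: 148 × 1.08 ≈ 160, or 80 per arm.

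**Inputs**
- Response 50% (ruxolitinib) and 30% (BAT), from Statistical planning.
- Flare rate f among responders, from Rationale for the trial (retrospective ruxolitinib series): 14/45 = 31% at the longer follow-up and 3/44 = 6.8% at the shorter one.
- Assumption: the same f applies on BAT. The article gives no BAT flare rate.
- c = share of BAT flares that lead to crossover. e = share of ruxolitinib flares managed by increase or restart. Neither is known.
- Assumption: BAT flares without crossover get no new agent, and ruxolitinib flares not re-escalated do get one.

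**Flares and counted events**

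Flares = 80 × response × f. Counted on BAT = flares × c. Counted on ruxolitinib = flares × (1 − e).

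- f = 14/45: flares 40 × 0.311 = 12.4 (ruxolitinib) and 24 × 0.311 = 7.5 (BAT).
- f = 3/44: flares 40 × 0.068 = 2.7 and 24 × 0.068 = 1.6.

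| f | c | e | Flares, ruxolitinib vs BAT | Counted as written |
|---|---|---|---|---|
| 31% | 1 | 1 | 12.4 vs 7.5 | 0 vs 7.5 |
| 31% | 1 | 0.5 | 12.4 vs 7.5 | 6.2 vs 7.5 |
| 6.8% | 1 | 1 | 2.7 vs 1.6 | 0 vs 1.6 |
| 6.8% | 1 | 0.5 | 2.7 vs 1.6 | 1.4 vs 1.6 |

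At f = 31% and full use, the component reads 0% vs 9.3% of the arm as written, and 15.6% vs 9.3% if flares are counted alike. The ruxolitinib arm has more flares here only because it has more responders at risk (40 vs 24). The reversal concerns this flare count, not FFS as a whole.

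**Equal true rates.** If response r and flare rate f are the same in both arms, the spurious difference in counted events (BAT minus ruxolitinib) is 80·r·f·(c + e − 1). It favours ruxolitinib when c + e exceeds 1, vanishes at c + e = 1 and favours BAT below that.

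The simulation set identical true rates, 80 per arm, other failures at 30% (an assumption) and a nominal one-sided 5% test on the failure proportion. It gave these false findings in favour of ruxolitinib, for r = 30% and r = 50%:

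| c | e | f = 31% | f = 6.8% |
|---|---|---|---|
| 1 | 1 | 35% and 65% | 9% and 12% |
| 1 | 0.5 | 15% and 25% | 7% and 8% |
| 0.5 | 0.5 | about 5% | about 5% |
| 0.5 | 0 | about 1% and 0.4% | 4% and 3% |

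This tests a simple composite proportion, which is not the planned analysis. It shows sensitivity to c and e and does not predict the trial's error rate.

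**The case against.** The wording of the rule is the same in both arms: raising or restarting an existing BAT agent is not new IST either. Crossover is allowed, not required, and ruxolitinib may be increased, not must. A BAT flare handled without a new agent is no event, and a ruxolitinib flare given a new agent is one. This stands. It makes the bias conditional and not certain.

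Re-escalation is described only for signs that reappear during or after tapering, so not every ruxolitinib flare qualifies. Some of the 14 patients in the series may have been re-treated with other agents. This also stands, and makes 12.4 an upper illustration.

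Failure types are analysed separately, so the direct effect is confined to the new-IST component. That is correct. It locates the problem without removing it, and because new IST competes with the other failure types, the other components can shift too.

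A reader might infer more from the other switching rules, in two ways.

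- **Day-28 non-response.** Ruxolitinib non-responders "will discontinue ruxolitinib and will be treated at the discretion of the investigator", so one might suppose their failures go uncounted while BAT crossovers count. But any new agent given to them is an event, and crossover on BAT is optional. If one quarter of non-responders in each arm got no new agent (an assumption), the missed failures would be 40 × 0.25 = 10 on ruxolitinib and 56 × 0.25 = 14 on BAT, the opposite direction. Adding 10 missed failures to 12 flares, to claim 22 of 80 ruxolitinib patients misclassified, applies the quarter to one arm only.
- **Failure to taper steroids.** The article names it as a crossover trigger on BAT and gives no counterpart on ruxolitinib. Silence in a condensed article shows nothing. A ruxolitinib patient given new IST for this reason is an event, and a separate secondary endpoint counts failure to taper alike in both arms.

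**Conclusion.** The concern holds for flares after response, within the new-IST component of FFS. On a plain reading, crossover is new IST and increasing or restarting ruxolitinib is not, and nothing in the article corrects for this in FFS. Whether a restart after a completed taper could be called new is undefined.

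The size is uncertain. It runs from nearly nothing (low flare rate, or half of flares in each arm taking these paths) to a component that counts none of about 12 ruxolitinib flares and all of about 7 BAT flares. These figures rest on the planned response rates, an equal flare rate in both arms, and assumed use of the optional paths. The documents do not support saying that every switching rule favours ruxolitinib, or that FFS as a whole must. The primary day-28 response rate and its sample size are untouched. The point is worth correcting because the trial's own duration-of-response definition already avoids it.

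**What to change.** Define the GvHD-failure component of FFS by disease state, identically in both arms: the first of aGvHD relapse or progression after response, or addition of new systemic IST for GvHD. State that crossover counts as new IST. State also that a flare managed by increasing or restarting any earlier systemic IST, including ruxolitinib, counts as failure.

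Do not make stopping the assigned treatment under the protocol an event. It is required of ruxolitinib non-responders at day 28, while crossover on BAT is optional, so this would build in a new asymmetry.

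Report the present definition, counting new IST only, as a sensitivity analysis, so that results stay comparable with other series.

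The cost is a somewhat lower FFS and one extra derivation. The article already schedules GvHD grading and GvHD medication at treatment and follow-up visits, so no new data are needed. The change concerns event counting only and alters no treatment rule.

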### Design

Our retrospective analysis demonstrated that ruxolitinib was active and could be safely administered in patients with steroid-refractory GvHD. Based on these data, this study will prospectively evaluate whether ruxolitinib as add-on to BAT is superior to BAT alone in SR-aGvHD. BAT follows current recommendations of the Onkopedia/DGHO guidelines for treatment of aGvHD [22].

The RIG-study is an open-label, multicenter, randomized two-arm phase II study in which patients are randomized to ruxolitinib and BAT versus BAT (Fig. 1). It is planned to randomize 160 patients for the study. Internet-based randomization to one of the two treatment groups is performed in a 1:1 ratio stratified by aGvHD grade (≤ grade 3 versus grade 4) and number of previous immunosuppressive treatments (≤ 3 versus ≥4). Patients will be recruited in 11 transplantation centers in Germany located in Berlin, Bonn, Cologne, Dresden, Freiburg, Hamburg-Eppendorf, Heidelberg, Homburg, Marburg, Munich, and Würzburg. All participating centers are highly experienced in the treatment of patients with aGvHD and stem cell transplantation.

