#### Inclusion criteria

For inclusion into the study, patients must fulfill all of the following criteria:Acute skin, intestinal or liver GvHD > grade 1 according to standard criteriaHistological confirmation in case of acute intestinal GvHDAge ≥ 18 yearsFailure of previous treatment, defined as presence of at least one of the following criteria:Treatment with prednisone/prednisolone/methylprednisolone in a dose of at least 2 mg/kg and lack of response after at least 7 days treatmentTreatment with prednisone/prednisolone /methylprednisolone in a dose of at least 2 mg/kg and progression after at least 3 days of treatmentFailure to taper the prednisone/prednisolone dose to 0.6 mg/kg/day or methylprednisolone dose to < 0.5 mg/kg/dayWritten informed consentAbility to understand the nature of the study and the study related procedures and to comply with them

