Binary secondary endpoints (e.g. proportion of patients with CR, proportion of patients dis-continuing treatment) will be estimated as rates and presented with exact two-sided 95% confidence intervals derived from the binomial distribution. Furthermore, the same type of logistic model using treatment assignment, aGvHD grade and number of immunosuppressive treatments as covariates will be applied.

OS and EFS probabilities will be estimated and displayed using the Kaplan Meier method.

The analysis of secondary time-to-event endpoints with competing risks (e.g. time to response, response duration, time to cGvHD development) will be performed by means of the Aalen Johanson estimator for the calculation of cumulative incidence rates. Appropriate Regression models (Cox models for OS, EFS, Fine and Gray models for endpoints with competing events) will be applied. For FFS, different types of failure will be analyzed separately, considering the other types of failure and onset of cGvHD as competing events. For evaluating QOL, scores will be calculated according to the EORTC QLQ-C30 Scoring Manual [24]. The scores at screening will be summarized and for different time points during follow-up, differences of the scores to the screening scores will be calculated in FAS and the PP set.

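### The stated model for taper failure and steroid discontinuation omits the steroid dose at randomisation, which two of the three entry routes leave open

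*Protocol article*

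**What the plan says.** **Entry.** The Inclusion criteria accept any one of three forms of steroid failure. The first is treatment "in a dose of at least 2 mg/kg and lack of response after at least 7 days". The second is progression after at least 3 days at the same minimum dose. Neither says when the course took place or what dose the patient takes at randomisation. The third is a failed taper, defined by nearly the same threshold as the later endpoint. The Discussion adds: "There is no limitation of previous and concomitant lines of aGvHD treatments".

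**Endpoints.** Three secondary endpoints concern steroids:
- taper failure, given as "Rate of patients in whom failure to taper steroids below methylprednisolone dose of 0.5 mg/kg/day", which "was observed within 56 days after randomization", or new immunosuppression because of that failure;
- "Discontinuation rate of steroid therapy for at least 4 weeks";
- "Cumulative steroid dose until day 56".

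The taper endpoint does not mention the dose at entry.

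**Analysis.** For binary secondary endpoints, Statistical planning says that "the same type of logistic model using treatment assignment, aGvHD grade and number of immunosuppressive treatments as covariates will be applied". Under Design, randomisation is "stratified by aGvHD grade (≤ grade 3 versus grade 4) and number of previous immunosuppressive treatments (≤ 3 versus ≥4"). Steroid dose appears in neither place. No model is stated for cumulative dose.

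**The concern.** Dose at entry should be a strong predictor of whether a patient is below a fixed dose by day 56 and of whether steroids are stopped for four weeks. A patient who starts at 2 mg/kg has far to go. A patient whose high-dose course failed several treatments ago may already be near or below the threshold, or off steroids.

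If entry doses vary this much, a model without them leaves avoidable variation in the comparison. Any chance difference in entry dose between arms then passes straight into the estimated treatment effect. Steroid sparing is a result that readers will look for in an add-on trial, so the estimate should not depend on such a difference when the data to remove it are at hand.

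**Working it through.** **1. What the entry routes imply for dose at randomisation**

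| Route (Inclusion criteria) | Dose required in the past | Dose at randomisation |
|---|---|---|
| No response after at least 7 days | at least 2 mg/kg | not set |
| Progression after at least 3 days | at least 2 mg/kg | not set |
| Failed taper | not set | not set; at or above the threshold when failure was declared |

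With no limit on earlier lines, and a stratum for four or more previous treatments, entry well after the high-dose course is allowed.

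**2. Threshold wording**

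| | Methylprednisolone | Prednisone/prednisolone |
|---|---|---|
| Inclusion criteria | < 0.5 mg/kg/day | 0.6 mg/kg/day |
| Secondary endpoints | below 0.5 mg/kg/day | < 0.6 mg/kg/day |

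A patient held at exactly 0.6 mg/kg/day prednisolone has reached the entry target but not the endpoint target.

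**3. The plan's own figure**

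The article gives no figure for any steroid endpoint. Its sample size for the primary endpoint reproduces (50% versus 30%, one-sided 5%, power 80%):

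n per arm = [1.645 × √(2 × 0.40 × 0.60) + 0.842 × √(0.25 + 0.21)]² / 0.20² = 73.1, so 74 per arm and 148 in total. Then 148 × 1.08 = 159.84, so 160. It serves here only to set 80 per arm.

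**4. Chance imbalance (illustration)**

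Let b be the share of patients below the threshold at entry. This is an assumption. The 95% range of the between-arm difference in b is ±1.96 × √[2b(1 − b)/80]:
- b = 10%: ±9 points
- b = 20%: ±12 points
- b = 30%: ±14 points

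Suppose the failure rate above the threshold averages 50% and is nil below it. At b = 20% an imbalance of 12.4 points then shifts the difference in taper failure by 0.50 × 12.4 = 6.2 points.

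**5. Dilution and the restricted analysis (illustration)**

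Assume failure of 60% versus 40% above the threshold, none below it, 80 per arm and a one-sided 5% level. Power = Φ(d/se − 1.645), with se = √[(p₁q₁ + p₂q₂)/n].

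| b | Rates, all patients | Difference | Power, all (80 per arm) | Power, at or above threshold (n per arm) |
|---|---|---|---|---|
| 0 | 60% v 40% | 20 points | 83% | 83% (80) |
| 20% | 48% v 32% | 16 points | 67% | 75% (64) |
| 40% | 36% v 24% | 12 points | 51% | 64% (48) |

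For b = 20%, all patients: se = √[(0.2496 + 0.2176)/80] = 0.0764, and 0.16/0.0764 − 1.645 = 0.449. Restricted: se = √(0.48/64) = 0.0866, and 0.20/0.0866 − 1.645 = 0.664. The risk ratio is 0.67 in every row. Setting failure to nil below the threshold makes these figures an upper illustration of the dilution.

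**The case against.** The strongest reply is that nothing here is biased. Allocation is randomised 1:1, entry dose balances in expectation, and the confidence interval already allows for chance imbalance. Number of previous treatments, which is both a stratification factor and a covariate, captures part of the mechanism. No power or effect target is stated for these endpoints, so no planned figure is missed. All of this stands. It limits the point to efficiency and chance imbalance, but it does not explain why a probable strong predictor should be left out of a model that the article does fix.

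Three stronger readings are tempting and are not supported:

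- *Patients who enter below the threshold count as successes and cannot fail.* The article does not say how they are counted. The wording suggests that a patient who enters and stays below is not a failure, but that is an inference. Every entrant has active disease above grade 1, and a later dose rise or new immunosuppression could still lead to failure.
- *All steroid endpoints are modelled without entry dose.* The stated model covers binary endpoints only. Cumulative dose has no stated model, and that may properly be left to the analysis plan.
- *The taper endpoint should be confined to patients above the threshold.* That subset is fixed at baseline and so is valid, but it drops randomised patients. Under the assumed rates it recovers less than half of the lost power (67% to 75%, against 83% without dilution).

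The number of patients affected may also be small if most enter while still on a high dose. The article does not settle this.

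**Conclusion.** The point holds in a limited form. Entry dose is left open by two routes, and the model fixed for binary secondary endpoints ignores it. The taper-failure and steroid-discontinuation comparisons therefore give up efficiency and are open to chance imbalance. They are not systematically biased. The day-28 response endpoint and the sample size of 160 are untouched.

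The size cannot be derived from the article, which gives neither an entry-dose distribution nor taper-failure rates. The imbalance and power figures rest on assumed shares and rates, and the dilution figures also on no failures below the threshold. They show the direction and a plausible order of size, not an estimate. The prednisolone threshold mismatch is certain from the text but minor, since it concerns only a patient at exactly 0.6 mg/kg/day.

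**What to change.** 1. Add steroid dose at randomisation, in mg/kg/day under one stated conversion between methylprednisolone and prednisolone, as a covariate beside the two stratification factors for taper failure and steroid discontinuation. Do the same for cumulative dose when its model is specified.
2. Keep the taper rate in all randomised patients and state how those already below the threshold at entry are counted. Add a supporting analysis in patients at or above the threshold at randomisation.
3. Reconcile the prednisolone threshold in the Inclusion criteria with that in the Secondary endpoints. This review does not say which is right.

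**Cost.** Wording only. GvHD medication is already evaluated at screening, and cumulative dose needs steroid dosing from randomisation in any case. The supporting analysis has a smaller denominator. The adjusted odds ratio becomes conditional on entry dose, so it will differ somewhat from one adjusted for the two factors alone, and the report should say so. Entering dose as a continuous term is safer than an above/below indicator, which could fail to fit if almost no one below the threshold fails.
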